### Trial profile (CONSORT flow) and baseline characteristics

The flow of participants through the study will be displayed according to Consolidated Standards of Reporting Trials (CONSORT) (see Fig. 1 for example), including numbers of participants for enrolment, allocation, follow-up and analysis.

**Fig. 1 Fig1:**
[figure not shown]
Participant flow

Participant characteristics will be displayed according to their baseline characteristics for each group. Characteristics will be displayed for both the randomised and the observational arms of the study and displayed for ease of comparison (see Tables 2 and 3 for examples).

### Primary analysis

The primary analysis will follow the intention-to-treat (ITT) principle. The primary outcome is the PRWE score at 12 months for the participants recruited to the randomised trial. The MD in PRWE scores between the surgical and non-surgical groups will be tested using a two-sample *t* test. The mean values, SDs, MDs and 95% CIs will be displayed (see Table 6 for example). The medians and inter-quartile ranges will be represented in a box plot (see Fig. 2 for example).

**Table 6 Tab6:** Primary and secondary outcomes at 12 months for the randomised group

Outcome		Randomised		
		Surgical (*n*=__)	Non-surgical (*n*=__)	Mean difference (95%CI)
PRWE				
DASH				
ED-5D-5D, mean (SD)	EQ-UI			
	EQ-VAS			
Pain on NRS (0-10)				
Patient-reported treatment success n(%)	Very successful			
	Successful			
	Neutral			
	Unsuccessful			
	Very unsuccessful			
Patient-reported bother with appearance n(%)	Not at all			
	Bothered a little			
	Bothered moderately			
	Very bothered			
	Extremely bothered			
Radiographic measures, mean (SD)	Dorsal angulation (degrees)			
	Radial tilt (degrees)			
	Ulnar variance (mms)			
	Articular step (mms)

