### Study population

Three hundred participants provided consent and were recruited to CROSSFIRE from 19 participating hospital sites: 164 participants in the randomised trial and 136 in the observational study. No patients declined participation in the observational study.

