### Randomisation and allocation

Randomisation occurred immediately after consent was gained by the recruiting orthopaedic team, within 1 week of the date of the injury. The orthopaedic team member contacted a central computer-based randomisation service by telephone. Participants were randomised using the method of minimisation. Randomisation was stratified by site, and minimisation, adjusting for gender and age (60–74 years and > 74 years), was employed as recommended by the National Health and Medical Research Centre (NHMRC) Clinical Trials Centre which provided the randomisation service.

Given the nature of the comparisons (surgery versus no surgery), it was not possible to blind the surgeon (study) investigators or participants. While this increases the risk of performance and detection bias, every effort was made to ensure that treatment, other than the interventions under study was otherwise identical in both groups. The primary outcome (PRWE score at 12 months) was collected from participants by blinded researchers, by telephone.

The statistician and the investigators conducting the analysis will remain blinded to the treatment groups. The dataset will be de-identified and treatment allocation will be masked using dummy group names (for example, Group A and Group B). De-identification and masking will be performed by an independent investigator who is not associated with the analysis. Masking of treatment allocation will be maintained until the statistical analysis and interpretation has been completed and two versions of the manuscript have been prepared and agreed to by all authors.

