### Power and sample size

We consider 14 points on PRWE to be the minimum clinical difference necessary to justify the additional costs of surgery compared to non-surgical treatment. This is the MCID determined by Sorensen [32] and larger than the 11.5-point estimate determined by Walenkamp [38].

A total of 128 patients (64 in each group) will provide 90% power to detect a difference of 14 points on the PRWE scale at a significance level of 0.05. We aim to recruit 160 patients to allow for 20% loss to follow-up. Two previous RCTs that had each published results at the time of our sample size calculation reported loss-to-follow-up rates of 19% [5, 39]. Given that this is a multi-centre trial, the closing date for recruitment (31 December 2018) was set based on expected recruitment of 160 randomised participants. However, by the time recruitment closed, 164 participants had been recruited.

The observational arm includes all eligible patients not consenting to randomisation. We recruited 136 participants to the observational arm to the trial.

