### Statistical analysis

#### Analysis principles

Data will be analysed using statistical analysis package SAS (SAS Institute Inc., Cary, NC, USA) and R statistical computing software [40].

Recruitment for CROSSFIRE concluded in January 2019. The final analysis will commence after the 12-month data collection is complete. The de-identified data-set will be inspected for missing data and data quality.

Study outcomes produce both continuous and categorical data. Continuous data will be inspected for normality. Continuous data will be presented by mean values and standard deviations (SDs) as well as mean difference (MD) and 95% confidence interval (CIs) (see Tables 4 and 5 as examples) if normally distributed, otherwise by median and interquartile range.

**Table 4 Tab4:** Secondary outcomes at 3 months for the randomised group

Outcome		Randomised		
		Surgical (*n*=__)	Non-surgical (*n*=__)	MD (95%CI) or odds ratio (95%CI)
PRWE, mean (SD)				
ED-5D-5L, mean (SD)	EQ-UI			
	EQ-VAS			
Pain on NRS (0-10)				
Patient-reported treatment success n(%)	Very successful			
	Successful			
	Neutral			
	Unsuccessful			
	Very unsuccessful			
Therapy utilisation up to 3 months (Yes/No) n(%)				
Therapy utilisation at 3 months (Yes/No) n(%)				
Radiographic measures, mean (SD)	Dorsal angulation (degrees)			
	Radial tilt (degrees)			
	Ulnar variance (mms)			
	Articular step (mms)

**Table 5 Tab5:** Secondary outcomes at 3 months for the observational group

Outcome		Observational		
		Surgical (*n*=__)	Non-surgical (*n*=__)	MD (95%CI) or odds ratio (95%CI)
PRWE, mean (SD)				
ED-5D-5L, mean (SD)	EQ-UI			
	EQ-VAS			
Pain on NRS (0-10)				
Patient-reported treatment success n(%)	Very successful			
	Successful			
	Neutral			
	Unsuccessful			
	Very unsuccessful			
Therapy utilisation up to 3 months (Yes/No) n(%)				
Therapy utilisation at 3 months (Yes/No) n(%)				
Radiographic measures, mean (SD)	Dorsal angulation (degrees)			
	Radial tilt (degrees)			
	Ulnar variance (mms)			
	Articular step (mms)			

Categorical data will be summarised according to frequency (*n*) and incidence (%) (see Table 5). Comparison between treatment groups will be tested using chi-squared and odds ratio with 95% CI.

Comparisons between treatment groups will be tested at the two-sided, 5% significance level. *P* values will be reported to three decimal places if *P* > 0.001. *P* values < 0.001 will be reported as < 0.001. Means and SDs will be reported to one decimal place.

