#### Data integrity

The study compares two treatments that comprise usual care. A Data Safety Monitoring Board (DSMB) was not required to be convened.

Interim analysis of data completeness and accuracy of data entry was conducted on two occasions during the data collection phase. The paper files from data collected by telephone were cross-checked against the electronic database. An audit of x-ray data was also be completed.

There are potential sources of bias. The types of bias and the efforts made to reduce their risk included:
Selection bias; randomisation occurs immediately after consent and immediately prior to treatment assignment using a central computer-based randomisation service by telephone, using stratification and minimisation to ensure balanced treatment allocation for site, age and genderPerformance bias; treatment, other than the interventions under study is identical in both groups. Participating surgeons have equipoise regarding the two treatment alternatives and were instructed not to express a treatment preference to the participants recruited to the randomised studyDetection bias; the primary outcome is collected from participants by blinded researchers, by telephone. The statistician and investigators will be blinded to the treatment group during the analysisAttrition bias; attempts are made to minimise missing data, such as obtaining multiple contact details at recruitment and using telephone follow up rather than mail. Interim analyses of data completeness and accuracy of data entry are conducted on two occasions in the data collection periodReporting bias; the de-identified participant-level dataset and statistical code will be made available for collaborative research projects. All pre-specified outcomes will be reported

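### The primary t test ignores the factors on which allocation was balanced (site, gender, age); if they predict PRWE, it is conservative and gives up some precision

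*SAP article*

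**What the plan says.** **Allocation.** Under Randomisation and allocation: "Randomisation was stratified by site, and minimisation, adjusting for gender and age (60–74 years and > 74 years), was employed". Data integrity gives the purpose: "using stratification and minimisation to ensure balanced treatment allocation for site, age" and gender.

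**Primary analysis.** "The MD in PRWE scores between the surgical and non-surgical groups will be tested using a two-sample" t test, by intention to treat, with means, SDs, the mean difference and its 95% CI. The Abstract names the same test. Analysis principles sets the level: "Comparisons between treatment groups will be tested at the two-sided, 5% significance level".

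**Elsewhere.** Secondary analysis uses the same t test for PRWE at 3 months and DASH at 12 months. Sensitivity analyses lists completed-case, as-treated and per-protocol analyses, none with covariates. Age and gender act as predictors of PRWE in one place only, the imputation model under Methods for handling missing data, which applies if more than 10% of the primary outcome is missing.

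**The concern.** A two-sample t test takes its standard error from the total within-arm variance, as if allocation had been simple randomisation. Here site, gender and age band were deliberately balanced, so whatever they explain of PRWE largely cancels from the difference in means. If they explain something, the t test's standard error is larger than the real sampling variation of the estimate. The test then rejects less often than 5% under the null, and the 95% CI covers more than 95%.

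The trial will be read from one mean difference and its CI, set against 14 PRWE points. An unnecessarily wide interval blurs both useful conclusions: that surgery is better, and that a 14-point benefit can be excluded. The plan already treats age and gender as informative about PRWE when it imputes the outcome, but not when it compares the arms.

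**Working it through.** **Inputs from the SAP article**
- Power and sample size: "A total of 128 patients (64 in each group) will provide 90% power to detect a difference of 14 points on the PRWE scale", at significance level 0.05; "We aim to recruit 160 patients to allow for 20% loss to follow-up".
- Study population: "Three hundred participants provided consent and were recruited to CROSSFIRE from 19 participating hospital sites: 164 participants in the randomised trial". That is 164/19 = 8.6 per site, and about 164 × 0.80 = 131 evaluable after 20% loss.

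**The plan's own figure.** 128/(1 − 0.20) = 160, so the recruitment target reproduces. The 128 cannot be checked independently because no SD is stated. Solving for it by the normal approximation: SD = 14 × √(64/2)/(1.960 + 1.282) = 24.4. The noncentral t gives 24.2, which is used below.

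**Assumption.** R² is the share of PRWE variance explained by site, age and gender together. The documents give no value, so a range of 0 to 30% is used.

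**Limiting case, perfect balance among those analysed.** The excess CI width is 1/√(1 − R²) − 1, and the type I error is 2 × [1 − Φ(1.96/√(1 − R²))].
- R² 5%: 2.6% and 4.4%.
- R² 10%: 5.4% and 3.9% (1.96/√0.90 = 2.066).
- R² 20%: 11.8% and 2.8%.

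These are upper limits on the fault. Small sites and loss to follow-up leave balance imperfect.

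**Simulation of this design.** 164 participants over 19 sites of unequal size; minimisation on gender and age band within site with a biased coin of 0.8; 20% lost at random; SD 24.2. Further assumptions are 85% women, 35% in the older band, and R² split 50/40/10 between site, age and gender. There were 5,000 null runs per R². The mixed model has age and gender as fixed effects and site as a random intercept. Half-widths are mean 95% CI half-widths in PRWE points.

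| R² | Type I error, t test | Type I error, mixed model | Half-width, t test | Half-width, mixed model | t test too wide by | Half-width, 18 fixed site indicators |
|---|---|---|---|---|---|---|
| 0 | 4.8% | 4.8% | 8.36 | 8.35 | about 0 | 8.68 |
| 5% | 4.4% | 5.0% | 8.35 | 8.19 | 2% | 8.47 |
| 10% | 4.1% | 4.6% | 8.34 | 8.00 | 4% | 8.23 |
| 20% | 3.4% | 4.4% | 8.33 | 7.58 | 10% | 7.76 |
| 30% | 3.3% | 5.1% | 8.31 | 7.12 | 17% | 7.25 |

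The excess width is the ratio of half-widths; for example 8.33/7.58 = 1.099. The Monte Carlo standard error of a type I error near 5% is √(0.05 × 0.95/5000) = 0.3 percentage points. A second simulation with the same numbers of participants and sites, minimisation and loss gave type I errors of 4.7%, 4.4% and 3.5% at R² of 5%, 10% and 20%, and the same excess widths of about 2%, 4% and 10%. Hence the ranges quoted.

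**Power at a 14-point difference** (3,000 runs; Monte Carlo standard error about 0.5 points), at R² of 0/5/10/20/30%:
- t test: 91.5/89.8/91.9/91.5/92.2%.
- Mixed model: 91.4/90.6/93.8/94.5/96.6%.

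**The case against.** The strongest reply is that the t test is prespecified, simple and valid. The mean difference is unbiased, type I error stays at or below 5%, and simulated power is about 90–92%, so the planned 90% is essentially met. The gain in half-width is 0.16, 0.34 and 0.75 points at R² of 5%, 10% and 20%, against a 14-point threshold, and without a figure for R² it could be nil. All of this stands. It limits the size of the point but does not remove it: the stated test does not match the stated allocation, and matching it costs almost nothing.

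Four stronger readings are tempting, and the documents do not support them.
- A reader might infer that the CI and p value are certainly too conservative. That requires R² above zero, which the documents do not establish.
- A reader might infer that the test is invalid or the trial underpowered. The error is in the safe direction and power holds.
- A reader might take the perfect-balance figures (type I error 2.8%, CI 11.8% too wide at R² 20%) as the size of the fault. With 19 sites and 20% loss they overstate it.
- A reader might think any adjustment is free. Eighteen fixed site indicators widen the CI at R² of 5% or less (8.68 against 8.36 at zero; 8.47 against 8.35 at 5%).

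The article rests on version 11 of the SAP, which is not shown. A supporting adjusted analysis may be described there, so the point concerns the primary test as the article states it.

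**Conclusion.** The point holds as one of calibration and efficiency, conditional on site, age and gender being prognostic for PRWE. With R² assumed at 5%, 10% and 20%, the t test's type I error is about 4.4–4.7%, 4.1–4.4% and 3.4–3.5%, and its CI is about 2%, 4% and 10% too wide. At R² of zero there is no loss. The direction follows from the design. The size rests on the assumed R², the implied SD of 24.2, 20% loss at random and the assumed form of the minimisation. The change is worth making because the random-intercept model is essentially free even if the factors explain nothing (half-width 8.35 against 8.36).

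**What to change.** Make the primary analysis a linear mixed model for 12-month PRWE, with randomised group, age and gender as fixed effects and site as a random intercept rather than 18 site indicators. State in advance whether age enters in years or in the two minimisation bands (the simulation used bands). Report the adjusted mean difference and 95% CI. Fit the same model within each dataset if multiple imputation is triggered. Keep the t test as a supporting analysis, and use the same covariates for 3-month PRWE and 12-month DASH.

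Fracture type was not a balancing factor. Adding it is optional and would rest on precision alone.

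The cost is a change of wording. Age and gender are baseline data and site is known from the stratified allocation, so nothing new is collected. The article places the final analysis after 12-month data collection with treatment groups masked, so the change can be made without knowledge of results.

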**Fig. 2 Fig2:**
[figure not shown]
Box plot of primary outcome

### Secondary analysis

Outcomes for the randomised group and the observational group will be analysed and represented separately. Outcomes gathered at 3 months will be displayed for the randomised group (see Table 4) and for the observation group (see Table 5). Outcomes gathered at 12 months will be displayed for the randomised group (see Table 6) and for the observational group (see Table 7). Continuous outcomes will be reported by mean values as well as the MDs and 95% CIs. Categorical outcomes will be reported by frequency, incidence and odds ratios.

**Table 7 Tab7:** Primary and secondary outcomes at 12 months for the observational group

Outcome		Observational		
		Surgical (*n*=__)	Non-surgical (*n*=__)	Mean difference (95%CI)
PRWE				
DASH				
ED-5D-5D, mean (SD)	EQ-UI			
	EQ-VAS			
Pain on NRS (0-10)				
Patient-reported treatment success n(%)	Very successful			
	Successful			
	Neutral			
	Unsuccessful			
	Very unsuccessful			
Patient-reported bother with appearance n(%)	Not at all			
	Bothered a little			
	Bothered moderately			
	Very bothered			
	Extremely bothered			
Radiographic measures, mean (SD)	Dorsal angulation (degrees)			
	Radial tilt (degrees)			
	Ulnar variance (mms)			
	Articular step (mms)			

The MDs of PRWE measured at 3 months between the surgical and non-surgical groups will be tested using two-sample *t* tests. The MDs of DASH measured at 12 months between the surgical and non-surgical groups will be tested using two-sample *t* tests.

Physical therapy utilisation up to and at 3 months will be analysed. If surgical treatment is shown to be superior, a cost-effectiveness analysis will be conducted incorporating therapy utilisation and published separately to this analysis. For the purpose of this analysis, therapy utilisation up to 3 months (Yes/No) and ongoing therapy utilisation at 3 months (Yes/No) will each be reported in terms of frequency, incidence and odds ratio between each treatment group. See Tables 3 and 4 as examples.

Complications will be reported in terms of frequency, incidence and the odds ratio between each treatment group (see Tables 8 and 9 as examples). Odds ratio will be calculated based on the number of participants for whom data is available.

**Table 8 Tab8:** Complications for randomised group

Complication; frequency (incidence)	Randomised group		
	Surgical (*n* = _)	Non-surgical (*n* = _)	Odds ratio (95% CI)
Deep infection	*n* (%)	*n* (%)	
Reoperation	*n* (%)	*n* (%)	
Neuropathy	*n* (%)	*n* (%)	
Tendon irritation requiring treatment	*n* (%)	*n* (%)	
Tendon rupture	*n* (%)	*n* (%)	
Fracture non-union at 6 months	*n* (%)	*n* (%)	
Implant failure	*n* (%)	*n* (%)	
CRPS	*n* (%)	*n* (%)	
Death	*n* (%)	*n* (%)	
Any complications	*n* (%)	*n* (%)	

*CI* confidence interval, *CRPS* chronic regional pain syndrome

**Table 9 Tab9:** Complications for observational group

Complication; frequency (incidence)	Randomised group		
	Surgical (*n* = _)	Non-surgical (*n* = _)	Odds ratio (95% CI)
Deep infection	*n* (%)	*n* (%)	
Reoperation	*n* (%)	*n* (%)	
Neuropathy	*n* (%)	*n* (%)	
Tendon irritation requiring treatment	*n* (%)	*n* (%)	
Tendon rupture	*n* (%)	*n* (%)	
Fracture non-union at 6 months	*n* (%)	*n* (%)	
Implant failure	*n* (%)	*n* (%)	
CRPS	*n* (%)	*n* (%)	
Death	*n* (%)	*n* (%)	
Any complications	*n* (%)	*n* (%)	

*CI* confidence interval, *CRPS* chronic regional pain syndrome

Repeated measures analysis will be used for the following:
Continuous variables measured at 3 months and 12 months include EQ-5D-5L (UI and VAS scores), pain on NRS (0–10) and radiographic measures (dorsal angulation, radial tilt, ulnar variance and articular step). These measurements will be analysed using analysis of variance (ANOVA) with repeated measuresCategorical variables measured at 3 months and 12 months include patient-reported treatment success (Likert) and patient-reported bother with appearance (Likert). See Additional file 1 for question format. These variables will be analysed by contingency table to compare the frequency of treatment success categories between the two randomised groups. Results will be displayed as odds ratio with 95% CIs (see Table 4 for example)

The observational group will be used to investigate potential selection bias. Baseline characteristics will be compared between the observational group and the randomised group (see Table 10 for example).

**Table 10 Tab10:** baseline characteristics for the randomised and observational arms of trial

Baseline measure		Randomised arm (*n*=__)	Observational arm (*n*=__)
Age (years), mean (range)			
Gender n (%)	Female		
	Male		
Fracture type n (%)	23A		
	23C		
Radiographic features, mean (SD)	Dorsal angulation (degrees)		
	Radial tilt (degrees)		
	Ulnar variance (mms)		
	Articular step (mms)		
Co-morbidities, n (%)	Diabetes? (Y/N)		
	Smoker? (Y/N)		
	Glucocorticoid treatment? (Y/N)		
	Osteoporosis treatment? (Y/N)		

The 2-, 5- and 10-year outcomes will be analysed separately to this analysis and will be published at a later date.

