## Methods/design

### Design

CROSSFIRE is a prospective, multi-centre study with 19 sites in Australia and New Zealand. The study includes a randomised, comparative-effectiveness trial and a parallel observational study; eligible patients were invited to participate in the randomised trial in which their treatment was randomised to surgical or non-surgical treatment. Eligible patients who declined to participate in the randomised study were invited to join the observational study. Participants in the observational study received standard care (one of the two treatment arms in the randomised trial) according to patient and surgeon preference and had the same outcomes measured at the same timepoints as those participating in the randomised trial.

We included an observational ‘preference’ arm that followed non-randomised patients in a similar manner to randomised participants to investigate potential selection bias and provide information on the generalisability of the study [19]. This study design has been used in surgical trials [20] and has been recommended as a model for trials of surgery versus non-surgical treatment where recruitment rates are expected to be lower than for other randomised controlled trials (RCTs) [21].

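### Preference-treated observational patients are compared by unadjusted mean differences and odds ratios, with no descriptive-only label, so those contrasts cannot be read as treatment effects

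*SAP article*

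**What the plan says.** The Design section states that observational participants "received standard care (one of the two treatment arms in the randomised trial) according to patient and surgeon preference". It gives the reason for following them as "to investigate potential selection bias and provide information on the generalisability of the study".

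The Secondary analysis section then sets out the outcome comparisons. "Outcomes for the randomised group and the observational group will be analysed and represented separately". For both cohorts, "Continuous outcomes will be reported by mean values as well as the MDs and 95% CIs", and "Categorical outcomes will be reported by frequency, incidence and odds ratios". The table shells carry this through for the observational group:

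- Table 5 (3 months) has a column for a mean difference or odds ratio with 95% CI.
- Table 7 (12 months, including PRWE) has a mean-difference column with 95% CI.
- Table 9 (complications) has an odds-ratio column with 95% CI.

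The named tests are unadjusted. "The MDs of PRWE measured at 3 months between the surgical and non-surgical groups will be tested using two-sample" *t* tests, and the same holds for DASH at 12 months. Under Analysis principles, for categorical data, "Comparison between treatment groups will be tested using chi-squared and odds ratio with 95% CI". The repeated-measures ANOVA planned for quality of life, pain and radiographic measures names neither a cohort nor covariates.

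For selection bias the plan specifies one analysis: "The observational group will be used to investigate potential selection bias. Baseline characteristics will be compared between the observational group and the randomised group", shown in Table 10.

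**The concern.** Where patient and surgeon choose the treatment, the two treatment groups may differ in age, fracture pattern, displacement or co-morbidity, and each of these may bear on wrist function. An unadjusted mean difference or odds ratio then mixes any effect of surgery with the reasons for choosing it. The 95% CI beside it covers sampling error only.

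Table 7 uses the same layout as Table 6 for the randomised group, so readers will compare the two. If the estimates agree, the observational arm may be taken to confirm the trial. If they differ, confounding cannot be told apart from a real difference in effect between the cohorts. No sentence in the article warns against either reading. The variables needed to do better (age, gender, fracture type, radiographic features and healing risk factors) are collected at baseline, but in this arm they are used only for description, in Tables 3 and 10.

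**Working it through.** **1. The text side by side.** Design: treatment by preference. Secondary analysis and Tables 5, 7 and 9: surgical v non-surgical contrasts with 95% CIs. Analysis principles, Secondary analysis and Sensitivity analyses: no regression, propensity, stratified or weighted method for the observational arm, and no statement that its contrasts are descriptive. The point rests on this step. The arithmetic below only gives a sense of scale.

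**2. The plan's own figures.** Power and sample size gives 64 per group, 90% power, a 14-point difference and a significance level of 0.05 (two-sided under Analysis principles), and 160 recruited for 20% loss.
- 128 / (1 − 0.20) = 160, which reproduces.
- No SD is stated, so 64 per group cannot be reproduced independently. Solving backwards, SD = 14 × √(64/2) / (1.960 + 1.282) = 24.4; with the noncentral *t* distribution it is 24.2. I use 24.2 as an assumption for both cohorts.

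**3. Precision of the observational contrast.** Assume 20% loss: 136 × 0.80 ≈ 109 evaluable. The split by treatment is not stated, so two are shown.
- 54 and 55: SE = 24.2 × √(1/54 + 1/55) = 4.64; 95% half-width about 9.2 points.
- 33 and 76: SE = 24.2 × √(1/33 + 1/76) = 5.05; 95% half-width about 10.0 points.

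**4. Possible bias.** The documents hold no confounder data, so the inputs are assumed. For one binary confounder, bias = (its effect on PRWE) × (difference in its prevalence between treatment groups). With no true treatment effect, the chance that the 95% CI excludes zero follows from the noncentral *t* distribution with noncentrality bias/SE.

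| Effect on PRWE | Prevalence difference | Bias | CI excludes 0, equal split | CI excludes 0, 30/70 split |
|---|---|---|---|---|
| 5 | 0.10 | 0.5 | 5.1% | 5.1% |
| 10 | 0.30 | 3.0 | 9.8% | 9.1% |
| 15 | 0.40 | 6.0 | 25% | 21.8% |

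The range therefore runs from negligible to 6/14 = 43% of the clinically important difference. Several confounders could add up or cancel.

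**5. Comparing the treatment effect between cohorts.** Assume 80% follow-up (164 × 0.80 ≈ 131 and 136 × 0.80 ≈ 109) and equal treatment splits.
- SE = 24.2 × √(4/131 + 4/109) = 6.3 points.
- 95% half-width = 1.96 × 6.3 ≈ 12.3 points, close to the 14-point threshold.

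**6. How much adjustment the data can carry.** Age, gender, fracture type, four radiographic measures and four co-morbidity items make 11 terms. Nineteen sites add 18, giving 29 terms for about 109 people, or fewer than four per term. Five covariates plus treatment make six terms, about 18 people per term.

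**The case against.** Several points on the other side are sound.

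- **The observational arm still serves its selection-bias aim.** A reader might infer that it cannot inform generalisability at all. The documents do not support that. The Abstract describes the selection-bias assessment as a comparison of participants between the arms, Table 10 delivers it, and confounding within the observational arm does not touch it. Outcome levels within each treatment also carry some information. Nor does the plan promise to estimate whether the treatment effect differs between cohorts.
- **Confounding is a risk here, not a finding.** A reader might infer that Tables 5, 7 and 9 are bound to be biased by a material amount. No observational baseline data are given, so neither size nor direction is known. Table 3 will show measured imbalance by treatment, although it will not correct for it.
- **The testing planned for this arm is ambiguous.** A reader might infer that every randomised-arm test is repeated. The 12-month PRWE *t* test is limited to participants in the randomised trial, the Likert contingency analysis names the two randomised groups, the sentences on 3-month PRWE and 12-month DASH name no cohort, and the observational tables have no p-value column. The contrasts with 95% CIs are nevertheless explicit for this arm.
- **The article rests on a signed version 11 that is not shown.** Model detail could sit there. But the article itself states the effect measures for this arm; this is not merely silence.
- **Heavy adjustment would fail.** Site and the full covariate list are too much for about 109 people, and regression is not workable for infrequent complications. The fix is limited accordingly.

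**Conclusion.** The concern holds in limited form. The plan specifies unadjusted surgical v non-surgical contrasts with 95% CIs in a cohort treated by preference, and neither adjusts them nor marks them as descriptive. As written, they cannot be read as treatment effects or as a check that the randomised effect generalises. The randomised primary analysis and Table 10 stand.

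The size cannot be determined from the documents. The 0.5 to 6 point range is illustrative: it rests on assumed confounder strengths and, for the exclusion rates, on a back-solved SD of about 24.2, 80% follow-up and assumed treatment splits. This is a worthwhile, low-cost improvement to a secondary analysis and does not threaten the trial's main conclusion.

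**What to change.** Before treatment labels are unmasked:

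1. For the continuous outcomes in the observational arm, 12-month PRWE first, report a regression-adjusted mean difference with 95% CI. Fix a short covariate list in advance from baseline variables already collected, for example age, gender, fracture type, and dorsal angulation and ulnar variance at presentation.
2. Label the unadjusted figures in Tables 5 and 7, and all of Table 9, as descriptive, with no p values or between-group inference. Do not attempt adjusted odds ratios for infrequent complications. Table 9's column heading names the randomised group and should be corrected at the same time.
3. State that the two-sample *t* tests and chi-squared tests apply to the randomised cohort only.
4. Optionally, add a treatment-by-cohort estimate for 12-month PRWE with its 95% CI, labelled exploratory.

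The cost is a little more analysis on existing data. Residual confounding will remain, and the cohort comparison will be imprecise (about ±12 points under the assumptions above). Both should be stated as limitations.
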